## Abstract

Stroke remains a leading cause of disability and mortality in Bangladesh, with limited data on risk stratification models tailored to the local population. Current prediction models inadequately capture the complex interplay of socioeconomic, environmental, and mental health factors prevalent in Bangladesh. This study protocol was designed to develop an artificial intelligence (AI)-based risk prediction model for stroke occurrence and poor long-term outcomes, specifically for the Bangladeshi population. The Foresighting Outcomes and Risk Evaluation with Computational Artificial Intelligence in Stroke Trials (FORECAST) study is an ambispective case-control study that will enroll 4,000 participants (2,000 stroke cases and 2,000 controls) from the National Institute of Neurosciences and Hospital, Bangladesh, between May 2022 and April 2026. We will develop ensemble machine learning models using comprehensive phenotypic data, including sociodemographic variables, comorbidities, anxiety/depression scores, and clinical parameters. The study will employ explainable AI techniques to enhance clinical interpretability and validation through k-fold cross-validation methods. The FORECAST study will establish the first AI-based stroke prediction model for Bangladesh, accounting for unique local risk factors, including rural-urban disparities and mental health comorbidities, with expected accuracy exceeding 90% based on recent advances in stroke prediction modeling. This study addresses critical gaps in stroke risk assessment for Bangladesh and similar low-middle-income countries by incorporating culturally relevant risk factors into advanced machine learning frameworks.

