Inclusion criteria encompass complete medical records availability and Bangladeshi residency for ≥5 years, while exclusion criteria include incomplete clinical data and previous stroke history for first-ever stroke analyses. Cases include adult patients (≥18 years) with acute ischemic or hemorrhagic stroke confirmed by a neuroimaging scan, either a CT/MRI scan, evaluated by two experts (neurologist and intervention radiologist). Stroke diagnosis will follow American Stroke Association (ASA) guidelines, confirmed by clinical evaluation and CT or MRI imaging. All patients with any form or severity of stroke, including mild, severe, prior, recurrent, critically ill, or intubated cases, will be included to reduce selection and reporting bias. Individuals with major comorbidities, such as other neurological disorders (e.g., brain tumors), severe systemic illnesses (e.g., cancer), secondary strokes due to other conditions (e.g., endocarditis, trauma), or those taking medications affecting stroke risk, will be excluded. Controls comprise age and sex-matched healthy adults without stroke history, recruited from hospital visitors and community health facilities, ensuring representative sampling across urban and rural populations. Controls will be 18 years or older, have no history of stroke, and must provide written informed consent. Hospitalized individuals are not eligible as controls. If spouse controls are unavailable, age- and sex-matched community volunteers will be recruited, with gender balance ensured through equal representation or sex stratification in analysis. The study will maintain equal proportions of males and females in both groups to address sex-related differences in stroke risk. Controls will be selected from the same geographic and socioeconomic backgrounds as cases to minimize population stratification and ensure comparability in environmental factors, lifestyle, and medication use.

The study will enroll 4,000 participants, comprising 2,000 stroke cases and 2,000 matched controls. Sample size calculations utilized established formulas for case-control studies with binary exposure, assuming 80% power, 5% significance level, and expected stroke prevalence of 35% in the exposed group versus 15% in the unexposed group [12,13]. This sample size ensures adequate power to detect clinically meaningful associations while accounting for potential data missingness and subgroup analyses. The formula for case-control studies with binary exposure:

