n = [P₁(1-P₁) + P₀(1-P₀)] × (Zβ + Zα/2)² / (P₁ - P₀)²

where power (1-β): 80% (Zβ = 0.84); α: 5% (Zα/2 = 1.96), expected stroke prevalence in exposed group (P₁): 35%, expected stroke prevalence in unexposed group (P₀): 15%, and minimum detectable odds ratio: 2.0.

Calculation:

n = [0.35×0.65 + 0.15×0.85] × (0.84 + 1.96)² / (0.35 - 0.15)²

n = [0.2275 + 0.1275] × 7.84 / 0.04

n = 0.355 × 196 = 69.58 ≈ 1,740 per group

Accounting for 15% loss to follow-up and missing data: 1,740 × 1.15 = 2,000 per group

The total sample size will comprise 4,000 participants, divided into 2,000 cases and 2,000 controls.

Comprehensive data collection encompasses sociodemographic variables (age, sex, education level, rural-urban residence, occupation, income), clinical parameters (blood pressure, glucose levels, lipid profiles, body mass index), comorbidities (hypertension, diabetes mellitus, atrial fibrillation, coronary artery disease), lifestyle factors (smoking, alcohol consumption, physical activity), and mental health assessments using validated instruments including the Generalized Anxiety Disorder-7 (GAD-7) and Patient Health Questionnaire-9 (PHQ-9) scales [14,15]. Outcome measures include stroke occurrence (primary outcome) and long-term functional outcomes assessed using the Modified Rankin Scale at 90 days post-stroke (secondary outcome) [16]. Additional outcomes encompass stroke recurrence, mortality, and healthcare utilization patterns to provide comprehensive prognostic information.

The study will implement an ensemble machine learning approach integrating multiple algorithms to optimize prediction accuracy [17]. The modeling framework comprises four specialized modules: a sociodemographic module utilizing neural networks for processing education, rural-urban status, and socioeconomic factors; a clinical risk module employing random forest algorithms for traditional risk factors; a mental health module using gradient boosting to capture anxiety-depression patterns; and an outcome prediction module combining all inputs for final risk stratification [18,19].

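### Controls are selected on factors the model is meant to learn: age and sex main effects for stroke occurrence cannot be learned, and those of residence and socioeconomic status are attenuated

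*Protocol article*

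**What the plan says.** All statements on control selection are in Materials and methods.

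- Age and sex: "Controls comprise age and sex-matched healthy adults without stroke history, recruited from hospital visitors and community health facilities". The same sentence goes on to promise that urban and rural populations will be sampled representatively.
- Sex again: "The study will maintain equal proportions of males and females in both groups to address sex-related differences in stroke risk".
- Spouses: "If spouse controls are unavailable, age- and sex-matched community volunteers will be recruited". This makes spouses the implied first choice and volunteers the fallback. The sentence adds that gender balance will come from equal representation or from stratifying the analysis by sex.
- Background: "Controls will be selected from the same geographic and socioeconomic backgrounds as cases to minimize population stratification". The stated aim extends to "ensure comparability in environmental factors, lifestyle, and medication use".

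The same section makes stroke occurrence the primary outcome and sets the primary objective as a model that identifies its independent predictors. Age, sex, education, residence, occupation and income are collected as sociodemographic variables. One of the four modules is "a sociodemographic module utilizing neural networks for processing education, rural-urban status, and socioeconomic factors". The Abstract describes the model as "accounting for unique local risk factors, including rural-urban disparities and mental health comorbidities".

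The Statistical analysis text names conditional logistic regression for the matched data, with subgroups by residence, education and age. The limitations in the Discussion do not mention the effect of control selection on these predictors.

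**The concern.** Choosing controls to resemble cases on a factor gives that factor a similar distribution in both groups whatever its true effect on risk. That is useful when the factor is a nuisance and the interest lies in other exposures. Here several of the selection factors are themselves target predictors.

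Two consequences follow for stroke occurrence. Conditional logistic regression cannot estimate the main effect of a factor on which pairs agree exactly. The planned correlation-based and mutual-information feature selection will tend to discard such factors, and SHAP values will then present their low importance as a finding. A reader could conclude that residence or income matters little for stroke in Bangladesh when the sampling produced that result. A tool meant for community screening would also lack the age and sex gradient it needs.

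**Working it through.** **Status of the numbers.** The article gives no effect sizes or population shares for these factors, so there is no stated figure to reproduce. The direction follows from the design. Every size below rests on assumed inputs.

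**Step 1: residence.** Let m be the fraction of controls matched on residence, a the rural share among cases and s the rural share in the source population. Then:

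- rural share in controls: q = m × a + (1 − m) × s
- observed odds ratio: [a/(1 − a)] ÷ [q/(1 − q)]

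With a = 0.70 and s = 0.50 (assumed), the case odds are 0.70/0.30 = 2.333.

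- m = 0: q = 0.50, OR = 2.333/1.000 = 2.33
- m = 0.5: q = 0.60, OR = 2.333/1.500 = 1.56
- m = 0.8: q = 0.66, OR = 2.333/1.941 = 1.20
- m = 1: q = 0.70, OR = 2.333/2.333 = 1.00

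To show the range, keep s = 0.50 and vary a:

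| a | m = 0 | m = 0.5 | m = 0.8 | m = 1 |
|---|---|---|---|---|
| 0.60 | 1.50 | 1.50/1.222 = 1.23 | 1.50/1.381 = 1.09 | 1.00 |
| 0.80 | 4.00 | 4.00/1.857 = 2.15 | 4.00/2.846 = 1.41 | 1.00 |

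The article does not fix m.

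**Step 2: age.** If risk doubled per decade (assumed), the 35 years between ages 40 and 75 would carry a risk ratio of 2^3.5 = 11.3. Age matching removes that marginal gradient from the training data.

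**Step 3: all factors together.** One simulated study of 2,000 cases and 2,000 controls used these assumed conditional odds ratios: rural 2.0, high education 0.5, high income 0.67, male 1.4, age about 1.8 per 10 years, hypertension 3.0. The last column is the AUC from the five sociodemographic variables alone.

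| Controls | Age/10 y | Sex | Rural | Education | Income | Hypertension | AUC |
|---|---|---|---|---|---|---|---|
| Unmatched | 1.73 | 1.37 | 1.83 | 0.45 | 0.66 | 2.83 | 0.78 |
| Matched on age, sex | 0.93 | 1.00 | 1.88 | 0.46 | 0.64 | 2.67 | 0.66 |
| + residence, income | 0.91 | 1.00 | 0.90 | 0.52 | 1.15 | 3.24 | 0.57 |
| + education | 0.92 | 0.98 | 1.01 | 0.98 | 0.99 | 2.95 | 0.50 |

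Each factor goes to about 1 once controls are matched on it, while hypertension, never matched on, stays near 3. Education largely keeps its effect until it is matched on. Matched factors can also cross 1 (age 0.93) because the fit adjusts for correlated predictors that were not matched.

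**Step 4: spouses and sex.** An opposite-sex spouse cannot be sex-matched to the case. Every such pair is discordant on sex, and the crude within-pair odds ratio is the number of pairs with a male case divided by the number with a female case. If cases are recruited half male and half female, that ratio is 1 by quota. Spouses also share a household and usually income, so those factors are rarely discordant within pairs.

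**The case against.** The strongest reply is that matching is ordinary case-control practice and that the background sentence may only mean drawing controls from the same source population. Much of this stands. Only age and sex are explicitly matched. No individual matching rule is given for geography or socioeconomic background, education is not named as a selection factor, and the promise of representative urban and rural sampling points the other way. The text therefore supports attenuation of unknown degree for residence and socioeconomic status, with an unresolved contradiction between the statements.

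A reader might infer four stronger things, none of which the document supports:

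- *That residence, income and education effects are removed outright.* That needs tight matching, which the article does not specify.
- *That the sociodemographic question cannot be answered at all.* Matching leaves interactions with unmatched exposures estimable, so the planned subgroups by residence, education and age can still show effect modification. Models of 90-day mRS, recurrence and mortality within cases do not depend on control selection.
- *That the model will give ages 40 and 75 the same risk.* Matching flattens the marginal age effect; the adjusted coefficient need not be zero and was below 1 in the simulation.
- *That the machine-learning models will use the pooled sample uncorrected.* The article is silent on weights and offsets, and an article may leave those to the full protocol or analysis plan.

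Spouse controls are also compatible with equal sex proportions at group level. Only the claim of individual sex matching fails for them.

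**Conclusion.** The point holds in limited form. For stroke occurrence, the main effects of age and sex cannot be learned from the case-control data. Those of residence and socioeconomic status, and indirectly education, are biased towards null to a degree set by an undefined rule and by the share of spouse controls. A null result or low feature importance for any of them would reflect the sampling and could not be read as evidence of no effect.

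The direction is certain. The size is not: the residence odds ratios, the 11.3-fold age ratio and the fall in sociodemographic AUC from 0.78 to 0.50 are illustrations on assumed inputs, and the 0.50 applies only if education is matched too. The matter should be settled before recruitment ends in April 2026, because each further control selected on background reduces what can be recovered.

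**What to change.** 1. **Control selection.** Reconcile the statements in Materials and methods. Keep representative urban and rural sampling. For remaining recruitment, drop selection on geographic or socioeconomic background beyond a common source population (the hospital's catchment), drop the preference for spouses, and frequency-match on age and sex only.
2. **Age and sex in the risk model.** Restore them from external age-sex stroke rates, added after fitting or with the coefficients fixed, or weight controls to the source population. An offset beside freely estimated age and sex terms does not work, because the free terms absorb it.
3. **Controls already selected on residence or socioeconomic status, including spouses.** Make no claim on those main effects or their feature importance. Limit sociodemographic claims for stroke occurrence to effect modification, and flag control type in the analysis.
4. **Spouse pairs.** Do not describe them as individually sex-matched, and adjust for age and sex in their conditional analysis.

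The cost is a change of protocol wording, an analysis change, and population or rate tables. The downsides are a mixed control pool after a change during recruitment, some dependence on external rates, and possible hospital referral differences in residence and socioeconomic status, which must be modelled and reported.

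### The stated minimum detectable odds ratio of 2.0 does not match its own inputs (35% versus 15% gives 3.05), and those inputs are labelled as stroke prevalence by exposure instead of exposure prevalence in cases and controls

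*Protocol article*

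**What the plan says.** All of this is in the Protocol article, Materials and methods, in the sample size text and the formula block after it.

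- The study is fixed at 4,000 participants, "comprising 2,000 stroke cases and 2,000 matched controls".
- The method is introduced as "The formula for case-control studies with binary exposure". The printed expression is n = [P₁(1−P₁) + P₀(1−P₀)] × (Zβ + Zα/2)² / (P₁ − P₀)².
- The planning proportions are described as "expected stroke prevalence of 35% in the exposed group versus 15% in the unexposed group". The input list under the formula repeats this definition for P₁ and P₀.
- The same list gives 80% power (Zβ = 0.84), 5% significance (Zα/2 = 1.96), "and minimum detectable odds ratio: 2.0".
- The odds ratio does not enter the formula, and no exposure prevalence among cases or among controls is given.

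**The concern.** Two things in this block do not fit together.

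First, two proportions determine an odds ratio. Once 35% and 15% are chosen, the odds ratio is no longer free, so listing 2.0 beside them is either an arithmetic slip or a figure from another calculation.

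Second, the formula is presented as the case-control one, and the groups being sized are cases and controls. The proportions compared between those groups are the shares exposed. The article instead labels P₁ and P₀ as the shares with stroke among exposed and unexposed people, which are cohort or cross-sectional quantities.

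At stake is what the article says the study can detect. It claims adequate power for clinically meaningful associations and aims to identify independent predictors of stroke. A reader weighing an association that is not found would take 2.0 as the limit of sensitivity, and the calculation does not support that value.

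**Working it through.** **Inputs, all from the sample size block:** P₁ = 0.35, P₀ = 0.15, Zβ = 0.84, Zα/2 = 1.96, stated odds ratio 2.0, group sizes 1,740 (before inflation) and 2,000 (enrolled).

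**1. Reproduce the plan's own figure.**
(0.84 + 1.96)² = 7.84, and 7.84 / (0.35 − 0.15)² = 7.84 / 0.04 = 196.
0.35 × 0.65 + 0.15 × 0.85 = 0.2275 + 0.1275 = 0.355.
0.355 × 196 = 69.58, so 70 per group. This matches the printed 69.58. The article then writes 1,740, which does not follow and is a separate matter.

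**2. Odds ratio of the inputs.**
(0.35/0.65) / (0.15/0.85) = 0.5385 / 0.1765 = 3.05.
The odds ratio is symmetric, so it is 3.05 whether the figures are stroke risk by exposure or exposure prevalence in cases and controls. The risk ratio is 0.35/0.15 = 2.33, so 2.0 is not a mislabelled risk ratio.

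**3. Is 2.0 the detectable odds ratio at a printed group size?** Hold P₀ = 0.15, read as control exposure, and solve the printed formula for P₁ at 80% power:

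| n per group | P₁ | Detectable odds ratio |
|---|---|---|
| 70 | 0.349 | 3.04 |
| 1,740 | 0.185 | 1.29 |
| 2,000 | 0.183 | 1.27 |

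None is 2.0.

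**4. What an odds ratio of 2.0 would need.**
With P₀ = 0.15, the odds are 2 × 0.15/0.85 = 0.30/0.85, so P₁ = 0.30/(0.85 + 0.30) = 0.30/1.15 = 0.261. The printed formula then gives n = 204.3, i.e. 205 per group.
With P₁ = 0.35 held instead, P₀ = 0.212 and n = 162.7, i.e. 163 per group.
So the value 2.0 does not explain 1,740 either. By the pooled version of the calculation, an odds ratio of 2.0 needs 2,398 per group at 1% control exposure and 1,221 at 2%. A requirement of 1,740 would therefore need a control exposure between 1% and 2%, which the article does not state.

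**5. Detectable odds ratio at the planned size.** The article gives no control exposure, so a range is assumed (printed formula, 80% power, two-sided 5%, matching ignored):

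| Control exposure (assumed) | 2,000 per group | 1,740 per group |
|---|---|---|
| 2% | 1.75 | 1.81 |
| 5% | 1.45 | 1.49 |
| 15% | 1.27 | 1.29 |
| 30% | 1.21 | 1.23 |

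**6. The labels.** If 35% and 15% were proportions within the enrolled sample, the overall share with stroke would be e × 0.35 + (1 − e) × 0.15 for an exposed fraction e, which lies between 15% and 35%. The design fixes that share at 50%, which would require e = (0.50 − 0.15)/0.20 = 1.75, an impossible value. This rules out the within-sample reading only.

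**The case against.** The strongest reply is that nothing in the study turns on the figure. The odds ratio is not in the formula, so replacing 2.0 by 3.05 changes no sample size, power or analysis. The main product is a prediction model judged on accuracy, AUC and calibration, and a single-exposure odds ratio decides none of these. This stands, and it limits the point to a correction of the stated justification.

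Three stronger readings are tempting and are not supported.

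- A reader might infer that the study is underpowered for an odds ratio of 2.0, because at 70 per group the power for it would be only about 37% with 15% control exposure. Nobody plans 70 per group. At 2,000 the detectable odds ratio at that exposure is about 1.27, so the printed 2.0 understates the sensitivity there.
- A reader might infer that 35% and 15% are impossible because half the sample has stroke by design. The article calls them expected prevalences and cites sources that are not available here, so they may be source-population values. That reading survives the 50% argument. It does not rescue the labels, because source-population risks are still not the proportions that a comparison of cases with controls estimates.
- A reader might infer that this mismatch accounts for the 1,740. It does not: inputs consistent with 2.0 give roughly 163 to 205 per group by the printed formula.

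It is also fair to say that 15% as a control exposure is an assumption of this check, and that the two-proportion formula ignores the planned matching and conditional logistic regression. Hence the range of exposures and the caveat.

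**Conclusion.** The point holds as an inconsistency in a stated design figure. An odds ratio of 2.0 is neither the one implied by 35% versus 15% (3.05, under either reading of the proportions) nor the detectable one at 70, 1,740 or 2,000 per group. P₁ and P₀ are also defined for a different comparison from the one the formula makes. Relabelling alone changes no number: the same 35% and 15%, read as exposure prevalences, still give 69.58 and 3.05.

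The 3.05 needs no assumption beyond the printed inputs. The detectable values rest on the assumed control exposures, on 80% power at two-sided 5%, and on an unmatched comparison of one binary exposure. Severity is moderate, since the planned size is not too small for an odds ratio of 2.0 at 15% exposure.

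**What to change.** 1. Define P₁ as the proportion exposed among cases and P₀ as the proportion exposed among controls, and name the exposure they refer to.
2. State the assumed odds ratio that matches them: 3.05 if 35% versus 15% is kept, or use 26.1% versus 15% if 2.0 is the target (about 205 per group by the printed formula, before inflation).
3. Report the minimum detectable odds ratio as a separate quantity at the enrolled size, over a range of control exposures as in the table above. Do not attach that label to 3.05, which is the effect assumed in the inputs and not the smallest one that 2,000 per group can detect.
4. Add that these values ignore the matching, or recompute them for the matched analysis.

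The cost is wording and one small table. Recruitment, data collection and analysis are unaffected. The step from 69.58 to 1,740 needs its own correction, and making it would not resolve this point.

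### The stated sample-size formula gives 70 per group, not 1,740, so the enrolment of 2,000 + 2,000 is not the result of the calculation shown

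*Protocol article*

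**What the plan says.** The calculation stands under Materials and methods in the Protocol article. The formula is "n = [P₁(1-P₁) + P₀(1-P₀)] × (Zβ + Zα/2)² / (P₁ - P₀)²". The inputs are "power (1-β): 80% (Zβ = 0.84"), "α: 5% (Zα/2 = 1.96"), "expected stroke prevalence in exposed group (P₁): 35"% and "expected stroke prevalence in unexposed group (P₀): 15"%. The same list adds a smallest detectable odds ratio of 2.0, which does not enter the formula.

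The substitution is written out and closes with "n = 0.355 × 196 = 69.58 ≈ 1,740 per group". The allowance for losses follows: "Accounting for 15% loss to follow-up and missing data: 1,740 × 1.15 = 2,000 per group". The total of 4,000 also appears in the Abstract.

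The text introducing the formula says of this size: "This sample size ensures adequate power to detect clinically meaningful associations while accounting for potential data missingness and subgroup analyses". No multiplier for subgroups, design effect or other adjustment is given apart from the 15%.

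**The concern.** One line sets 69.58 equal to 1,740, and the enrolment target is built on the second number. The article presents 4,000 as the size needed for 80% power to detect 35% versus 15%. If the formula needs only about 70 per group, that presentation is false. A reader then cannot tell what the study was sized to detect, or on what basis 4,000 was chosen. The listed odds ratio of 2.0 adds a second inconsistency, because it matches neither the two percentages nor what 2,000 per group can detect at the exposure levels examined below.

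**Working it through.** **Inputs**, all from Materials and methods: P₁ = 0.35, P₀ = 0.15, Zβ = 0.84, Zα/2 = 1.96, 15% loss, 1:1 allocation.

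**The plan's own figure**
- Variance term: 0.35 × 0.65 + 0.15 × 0.85 = 0.2275 + 0.1275 = 0.355.
- Squared sum of z values: (0.84 + 1.96)² = 7.84.
- Squared difference: (0.35 − 0.15)² = 0.04, and 7.84 / 0.04 = 196.
- n = 0.355 × 196 = 69.58, so 70 per group (69.66 with unrounded z values).

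The article's working is correct as far as 69.58. The value 1,740 is not reproduced.

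**Size of the gap**
- 1,740 / 69.58 = 25.0, and 1 / 0.04 = 25.
- 69.58 / 0.04 = 1,739.5, which rounds to 1,740. A second division by 0.04 would produce the printed figure, but that step is not shown.

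**Other standard calculations at 35% versus 15%, per group**
- Pooled variance, two-sided, 80% power: 73; with continuity correction: 83.
- One-sided: 57; with continuity correction: 67.
- Largest result over powers of 80% to 99%, one- or two-sided, with or without continuity correction: 178.

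None comes near 1,740.

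**Allowance for 15% loss on the correct base**
- 70 × 1.15 = 80.5, so 81 per group.
- 70 / 0.85 = 82.4, so 83 per group.
- In total, 162 to 166 rather than 4,000.

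**Power at the enrolled size.** Solving the same formula for the power deviate gives √(n × 0.04 / 0.355) − 1.96.
- n = 69.58: 2.80 − 1.96 = 0.84, which is 80% power, as intended.
- n = 1,700 (2,000 × 0.85): 13.84 − 1.96 = 11.88, essentially 100%.
- n = 2,000: 15.01 − 1.96 = 13.05, essentially 100%.

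**The odds ratio of 2.0**
- 35% versus 15%: (0.35/0.65) / (0.15/0.85) = 3.05.
- Odds ratio 2.0 from 15%: P₁ = 0.30 / (0.85 + 0.30) = 0.2609, and the article's formula gives 204.3, so 205 per group.

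**What the enrolled size can detect.** This uses the same formula with n = 1,700 and 80% power, solved for P₁. Here P₁ and P₀ are exposure proportions in cases and controls. The article gives no control exposure, so the P₀ values are assumptions chosen to show a range.

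| Assumed control exposure | Detectable case exposure | Odds ratio |
|---|---|---|
| 5% | 7.3% | 1.50 |
| 15% | 18.6% | 1.29 |
| 30% | 34.5% | 1.23 |

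The formula is for unmatched groups. The article plans matched controls and conditional logistic regression, so these odds ratios are approximations.

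**The case against.** The best defence is that the error enlarges the sample. With 2,000 per group, power for the stated contrast is far above 80%, so the claim of adequate power is not falsified for the main comparison. That stands. A reader might infer that the study is underpowered, or that enrolment should be cut; the documents support neither.

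It can also be said that the extra numbers cover subgroups. The article does name rural-urban, educational and age subgroups, so 70 per group was not its only stated need. But it attaches no figure to them, and its only adjustment is the 15%, applied after 1,740 has appeared. An approximation sign cannot carry a 25-fold allowance. Nor does the shortness of a journal article explain the problem: the calculation is printed in full and contradicts itself.

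Three stronger readings should be resisted:
- **That 0.04 was certainly divided out twice.** The figure fits, but working backwards from a chosen 2,000 fits about as well (2,000 / 1.15 = 1,739). The factor of 25 is fact; the cause is not.
- **That the 1.15 multiplier is a serious second error.** Dividing by 0.85 is the exact allowance, giving 2,047 from 1,740 against 2,001. The difference is about 2% and has no bearing once 1,740 is withdrawn.
- **That 4,000 was really chosen for developing a prediction model.** The article never says so.

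On the odds ratio, 2.0 would be roughly right at this sample size for a very rare exposure: the pooled formula needs 2,398 per group at 1% control exposure and 1,221 at 2%. The article names no such exposure, and its only percentages are 15% and 35%.

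**Conclusion.** The point holds and must be corrected. On the article's own formula and inputs, the requirement is 70 per group (81 to 83 with the 15% allowance). The printed 1,740 is 25 times too large, and 2,000 per group and 4,000 in total rest on it. That conclusion needs no outside assumption. The error is in the justification: the 4,000 is not the product of the stated 80% power calculation, and the odds ratio of 2.0 is inconsistent with 35% versus 15%. It is also inconsistent with the enrolled size over control exposures of 5% to 30%. The detectable odds ratios of 1.23 to 1.50 depend on those assumed exposures, on 15% loss and on an unmatched approximation.

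**What to change.** Rewrite the sample-size paragraph and leave enrolment as it is.

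1. Withdraw the equation of 69.58 with 1,740, and the step to 2,000 that depends on it.
2. State that the formula gives 70 per group for 35% versus 15%, and that 2,000 + 2,000 was not derived from it.
3. State what the fixed size delivers: with about 1,700 evaluable per group after 15% loss, 80% power for an odds ratio of about 1.29, 1.23 or 1.50 at assumed control exposures of 15%, 30% or 5%. Label this an unmatched approximation, because the analysis is matched.
4. For that statement, define P₁ and P₀ as exposure proportions in cases and controls. The article now defines them as stroke prevalence by exposure.
5. Replace the odds ratio of 2.0, or reconcile it with the percentages used.

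A statement of the precision that 4,000 gives the prediction model is optional. If added, it should be described as an assessment of a size already fixed, not as the original basis.

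The cost is the rewording of one paragraph, with no change to recruitment or data collection.

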**Figure 1 FIG1:**
[figure not shown]
Dummy flowchart showing case-control recruitment to dissemination GAD: generalized anxiety disorder; PHQ: Patient Health Questionnaire; AI: artificial intelligence; AUROC: area under the receiver operating characteristic curve; mRS: Modified Rankin Scale Image created by the authors

Statistical analysis

Statistical analyses will employ appropriate methods for case-control studies, including conditional logistic regression for matched data and multiple imputation for missing values. Subgroup analyses will examine risk patterns across rural-urban populations, educational strata, and age groups to identify population-specific risk factors. Model calibration will be assessed using Hosmer-Lemeshow goodness-of-fit tests and calibration plots [26].

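### The 15% loss allowance is applied as × 1.15 rather than ÷ 0.85, so 2,000 per group leaves 1,700 after that loss, not 1,740 (a minor error)

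*Protocol article*

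**What the plan says.** The protocol article, Materials and methods, works through a case-control formula with a binary exposure and arrives at 1,740 per group. It then inflates that figure: "Accounting for 15% loss to follow-up and missing data: 1,740 × 1.15 = 2,000 per group". The preceding paragraph presents the resulting size as giving adequate power while "accounting for potential data missingness and subgroup analyses".

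The primary outcome is stroke occurrence. The secondary outcome is the Modified Rankin Scale 90 days after the stroke. Stroke recurrence, mortality and healthcare utilisation are additional outcomes.

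Under Statistical analysis, the article plans methods suited to case-control data, "including conditional logistic regression for matched data", and multiple imputation for missing values.

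**The concern.** An allowance for loss is meant to leave the required number after the loss has occurred. The loss is taken from those enrolled, so the enrolled number must be the required number divided by the fraction retained. Adding 15% to the required number and then losing 15% of the larger total does not return to the starting point. The article's final step therefore claims protection that its own percentage does not give.

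The allowance also combines two kinds of loss. Whether a participant is a case or a control is fixed at entry, so loss to follow-up cannot remove anyone from the primary outcome. It can affect what is measured in cases afterwards. The line applies one figure to both groups without saying which analysis it protects.

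The inflation step is a separate slip from the derivation of 1,740. If only the base figure were corrected, the wrong multiplier would carry over to the new one.

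**Working it through.** **Inputs, all from the sample size paragraph:** 1,740 per group before the allowance; a 15% allowance; 2,000 per group after it; P₁ = 0.35 and P₀ = 0.15; Zα/2 = 1.96 and Zβ = 0.84.

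**1. The article's figure.** 1,740 × 1.15 = 2,001, stated as 2,000. The step reproduces as written.

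**2. What remains after a 15% loss.** 2,000 × (1 − 0.15) = 1,700. The shortfall against 1,740 is 40, and 40/1,740 = 2.3%.

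**3. What would be needed to keep 1,740.** 1,740/(1 − 0.15) = 2,047.1, rounded up to 2,048 per group. That is 48 more than planned (48/2,000 = 2.4%).

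**4. The loss that 2,000 does cover.** 1 − 1,740/2,000 = 13.0%.

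**5. Size in power terms.** Suppose 1,740 were exactly the size giving 80% power. At 1,700, power is Φ(2.8016 × √(1,700/1,740) − 1.9600) = Φ(0.809) = 79.1%, a loss of about one point.

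**6. Whether 1,740 is a real requirement.** The article's formula gives [0.35 × 0.65 + 0.15 × 0.85] × (0.84 + 1.96)² / (0.35 − 0.15)² = 0.355 × 7.84 / 0.04 = 69.58, so 70 per group. The article prints 69.58 and then equates it with about 1,740. That is a factor of 25 (69.58 × 25 = 1,739.5), for which no reason is given. With 35% against 15%, power is essentially 100% at 1,700 and at 1,740.

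The article also names a "minimum detectable odds ratio: 2.0", which its formula does not use. Its two percentages imply (0.35/0.65)/(0.15/0.85) = 3.05. For an odds ratio of 2.0, the requirement depends on exposure in controls, which the article does not give. Assuming 2% to 30% and an unpaired comparison, it runs from 1,221 down to 141 per group. Power at 1,700 is at least 91% across that range.

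**7. The same slip on the corrected base.** 70 × 1.15 = 80.5, so 81 enrolled, and 81 × 0.85 = 68.9 remain, below 70. Dividing gives 70/0.85 = 82.4, so 83 enrolled, and 83 × 0.85 = 70.6 remain.

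**The case against.** **The gap is trivial.** A shortfall of 40 per group costs about one point of power, and against the 70 that the formula gives it has no practical consequence. This stands, and it is why the point is minor and calls for no extra enrolment. The line remains wrong as written.

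**The 15% could be a mark-up on the required number.** On that reading 1,740 × 0.15 = 261 extra people are enrolled, and losing those 261 of 2,001 leaves 1,740. But 261/2,001 is a 13.0% loss, while the article describes its figure as a 15% loss. The reading accounts for the arithmetic but not for the wording.

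**A shared allowance is not wrong in itself.** The primary objective covers poor long-term outcomes as well as stroke occurrence, so some provision for follow-up loss is reasonable. This also stands. What is missing is a statement of which outcomes that provision concerns.

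**A stronger reading is tempting.** A reader might infer that the matched analysis would be left with about 1,445 pairs (2,000 × 0.85²) and would lose material power. The documents do not support this, for four reasons:

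- The figure needs strict 1:1 individual pairs, a 15% loss in each member that is independent of the partner, and deletion of incomplete records. The article calls the controls matched on age and sex but does not say that the analysis uses strict pairs. It says nothing about how losses fall within pairs.
- Multiple imputation is planned, so a missing covariate need not break a pair. Incomplete clinical data is also an exclusion criterion, so it is unclear how many incomplete records would count among the 2,000.
- Independence is not the extreme case. If losses never coincided within a pair, 2,000 − 300 − 300 = 1,400 pairs would remain. If they always coincided, 1,700 would.
- Part of the 15% is loss to follow-up, which cannot affect case or control status. Applying the whole 15% to the matched primary analysis would be inconsistent with that.

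A marked fall in power across these pair counts appears only if an effect smaller than the article's odds ratio of 2.0 is assumed.

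**Conclusion.** The point holds as a minor arithmetic error. The article's 15% loss, applied to its 2,000 per group, leaves 1,700 and not 1,740. Keeping 1,740 would take 2,048, and 2,000 covers 13.0%. These results need only the numbers in the quoted line and the ordinary meaning of a percentage loss from those enrolled.

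A reader might infer that the study is underpowered. It does not follow: 1,740 is not what the stated inputs require, so falling 40 short of it has no bearing on power for 35% against 15%. The unexplained move from 69.58 to 1,740 is the larger defect in the same paragraph, and both should be corrected together.

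**What to change.** Keep 2,000 per group and change the wording:

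- State that a 15% loss leaves 1,700 per group or, if 1,740 must remain, that 2,000 allows for a 13% loss.
- Use ÷ (1 − 0.15) in any recalculation. On the formula's own result this is 70/0.85 = 83 per group, not 81.
- Correct or justify the step from 69.58 to 1,740 in the same revision.
- State that loss to follow-up bears on the cases' follow-up outcomes, such as the 90-day Modified Rankin Scale, and not on case or control status.
- If a number of complete pairs is reported, give it as 1,400 to 1,700, conditional on 1:1 pairs, a 15% loss in each member and no imputation.

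The cost is a few sentences. No additional enrolment or change of design is needed, and the stated retained number becomes slightly smaller.
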